### Measurement of outcomes

The primary outcome will be self-reported depressive symptoms and remission rates, as measured by the PHQ-9 at 12-week post-intervention. Depression remission is defined as a PHQ-9 score < 5. The PHQ-9 is more specific for detecting depression in older adults [48] and is recommended for depression screening and severity assessment by the Chinese Society of General Practice, the Depressive Disorder Collaboration Group of Chinese Society of Psychiatry, the US Preventive Services Task Force, and others [17, 49, 50]. The consistency rate between PHQ-9 and Geriatric Depression Scale-15 (GDS-15) is 96.10% [51].

Secondary outcomes are additional health outcomes, cost-effectiveness, and potential mechanisms. Additional health outcomes include quality of life (measured by the World Health Organization Quality of Life-Older Adults, WHOQOL-OLD), physical activity levels, daily step counts, subjective sleep quality (measured by the Pittsburgh Sleep Quality Index, PSQI), objective sleep parameters including total sleep time (TST), wake after sleep onset (WASO), sleep onset latency (SOL), and sleep efficiency (SE), and anxiety symptom (measured by the Generalized Anxiety Disorder 7-item scale, GAD-7). Objective outcomes of physical activity levels, daily step counts, and objective sleep parameters will be obtained using a wrist-worn ActiGraph accelerometer for 7 consecutive days. This approach has been demonstrated to be effective among older adults in previous studies [52, 53].

For cost-effectiveness analysis, costs will be aggregated across all clusters using a bottom-up approach, and calculated individually for each cluster in the trial. The cost data for the economic evaluation will be collected from study records (e.g., personnel time, equipment, materials) and does not impose any additional data collection burden on the participants themselves. The economic evaluation will be conducted from a public healthcare system perspective. We plan to develop an intervention cost form for this purpose that covers and sums up all GESO-intervention costs and payments that would be reimbursed by health insurance companies if the respective intervention will be accepted for application in routine health care. All costs will be valued in Chinese Yuan (CNY), with prices adjusted to the 2024 value level. The cost-elements (e.g. wages of trainers, session or room cost, seminar documents, program development etc.) included into the calculation varied considerably depending on the various study-interventions or -programs. Cost of professional support will be estimated from relevant salary scales and published reports/literature. As the economic end point for the cost-utility analysis, we will consider the cost per quality-adjusted life year (QALY) gained. We will derive QALYs from the Five-level EuroQol Five-dimensional Questionnaire (EQ-5D-5 L) from T0 to T2 [54] using the norms for the urban Chinese population proposed by Yang [55]. In accordance with the China Guidelines for Pharmacoeconomic Evaluations (2020), we will discount both future costs and health outcomes (QALYs) at an annual rate of 5% for the base-case analysis, and employ discount rates ranging from 0% to 8% in sensitivity analyses to test the robustness of the results [56].

Saliva samples for the analysis of BDNF and irisin will be collected at baseline and at 12-week for biochemical assessments. To avoid the influence of circadian variation, sample collection will take place at the same time of the day, between 10:00 a.m. to 12:00 p.m. Participants will be asked to avoid food intake and oral chewing to prevent their effects on sample concentration. Before sample collection, participants will rinse their mouth with clean water and then drool into a 50mL enzyme-free centrifuge tube. Saliva samples will be centrifuged immediately at 10,000 rpm for 2 min, then, the supernatant will be collected and stored at −80℃. Saliva BDNF and irisin levels will be quantified by enzyme-linked immunosorbent assay (ELISA) using specific kits (BDNF kit: Cat. E-EL-H0010; Irisin kit: Cat. E-EL-H5735, Elabscience) following the manufacturer instructions.

EEG is a non-invasive, economical method to explore the electrocortical brain activity, and also has been applied to capture functional activity in interventional studies [57, 58]. Resting-state EEG data will be collected at baseline (T0) and post-intervention (T2) for exploring the neurophysiological mechanisms of the intervention. To facilitate participation and minimize burden, we will offer all participants flexible scheduling, transportation assistance or reimbursement to the lab, and a guided, relaxed assessment experience in a dedicated facility. EEG measurements will take place in a dimly lit room within the School of Psychology at Xinjiang Normal University. Participants will sit in a relaxed position, with their backs supported by the chair and both hands comfortably resting on a table in front of them. They will be instructed to perform an average of 12 min (10 to 15 min) eye-closed resting-state task followed by a 3-minute eyes-open resting condition. Data will be acquired using an ANT amplifier (Compumedics Neuroscan, SynAmps2,) equipped with a 64-channel active electrode cap arranged according to the international 10–20 system. Three electrooculogram (EOG) channels will be used to detect ocular artifacts. All signals will be referenced online to Cz and grounded at AFz, and digitized at a sampling frequency of 500 Hz. Electrode impedances will be maintained below 10 kΩ. Data will be processed and analysed with MATLAB R2024a (MathWorks, Natick, MA) in conjunction with the EEGLAB toolbox (v.2025.0.0) and custom-written scripts. All signals will be filtered using a 1 Hz high-pass filter, 80 Hz low-pass filter, and 50 Hz notch filter, then be down-sampled to 500 Hz.

Based on previous exploratory neurophysiological studies in older populations, we anticipated a good participation rate in this assessment. The resulting sample size for EEG analysis is expected to be sufficient for generating preliminary hypotheses regarding intervention-related neurophysiological changes, consistent with similar exploratory mechanistic studies. Study enrolment and assessment procedures are described in Table 1.

**Table 1 Tab1:** Schedule of enrolment and assessments

Timepoint	-T1	T0	T1	T2
	Enrolment and allocation	Baseline	6-week	12-week
Enrolment				
Eligibility screen	×			
Informed consent	×			
Allocation	×			
Assessment				
Demographic information		×		
Primary outcomes				
Depressive symptom: PHQ-9		×	×	×
Depression remission rate		×	×	×
Secondary outcomes				
Quality of life: WHOQOL-OLD		×		×
Physical activity: ActiGraph accelerometer measured levels and daily step counts		×		×
Subjective sleep quality: PSQI		×	×	×
Objective sleep: ActiGraph accelerometer measured TST, WASO, SOL, and SE		×		×
Anxiety symptom: GAD-7		×	×	×
Economic evaluation				
Costs				×
QALY: EQ-5D-5 L		×		×
Saliva collection (BDNF, irisin)		×		×
EEG		×		×

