### Sample size

Power calculation was performed using the PASS software module ‘Tests for Two Means in a Stepped Wedge Cluster Randomized Design’. Key input parameters were derived from a similar previous study [47], which reported a mean reduction in depressive symptom of 4.0 in intervention group compared to 2.0 in control group among community-dwelling older adults with depression. Based on our stepped-wedge design with 6 clusters, 2 clusters crossing over per sequence, an intra-cluster correlation (ICC) of 0.1, a planned sample size of 22 per community, a desired power of 90%, a two-side α level of 0.05, and an estimated 20% dropout rate, a total sample size of 165 participants will be required.

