The economic evaluation will include both cost-effectiveness analysis (CEA) and cost-utility analysis (CUA), considering only costs and effects occurring within the trial timeframe. CEA will assess the intervention effect on depression symptoms relative to costs in older adults. Results will be expressed as cost-effectiveness ratio (CER) and incremental cost-effectiveness ratio (ICER). CUA will be calculated by QALYs and cost-utility ratio (CUR). For the exploratory analyses of mechanistic outcomes, we will examine the intervention effects on the biomarkers (i.e., salivary BDNF and irisin levels) from baseline to post-intervention. Analyses of EEG data will be conducted on the subset of participants who complete this assessment and are therefore exploratory in nature. We will compare baseline characteristics between participants who do and do not complete the EEG to assess potential selection bias. Indicators including absolute power (AP), phase locking value (PLV), phase lag index (PLI), and weighted phase lag index (WPLI) will be analyzed to investigate potential neurophysiological mechanisms underlying the intervention’s effectiveness.

Primary analysis will follow the intention-to-treat (ITT) principle, including all randomized participants. Primary and secondary outcomes will be performed with generalized linear mixed models (GLMMs). Estimated intervention effects will be reported as mean differences for continuous outcomes or odds ratio for binary outcomes between intervention and control periods. To handle missing outcome data, we will employ multiple imputation by chained equations (MICE) under the assumption of missing at random. Sensitivity analyses will be conducted to assess the robustness of the findings by: (1) comparing results from the ITT analysis with those from a per-protocol (PP) analysis; (2) evaluating the impact of missing data under different assumptions (e.g., missing not at random scenarios); (3) adjusting for baseline depression symptom severity; and (4) using different depression classifications (i.e., the total score of PHQ-9 or the diagnostic criteria for depression based on DSM-IV [30, 62]). All analysis will be performed by an independent statistician using R software version 4.3.2 (R Core Team, R Foundation for Statistical Computing, Vienna, Austria, https://www.R-project.org). Statistical significance will be defined as a two-tailed *p*-value < 0.05.

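### Two primary outcomes (PHQ-9 score and PHQ-9 remission) share one 0.05 threshold with no success rule, and the sample size was calculated for the score only

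*Protocol article*

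**What the plan says.** The Measurement of outcomes section of the protocol article reads: "The primary outcome will be self-reported depressive symptoms and remission rates, as measured by the PHQ-9 at 12-week post-intervention". It then adds: "Depression remission is defined as a PHQ-9 score < 5". Remission is therefore a cut of the same score at the same time point.

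Table 1 treats the two as distinct. Under a plural heading for primary outcomes, one row is for the PHQ-9 depressive symptom score and a separate row reads "Depression remission rate".

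The Statistical analyses section gives each type of outcome its own effect measure: "Estimated intervention effects will be reported as mean differences for continuous outcomes or odds ratio for binary outcomes between intervention and control periods". It sets one threshold for the whole trial: "Statistical significance will be defined as a two-tailed *p*-value < 0.05". The article gives no order of testing, no division of alpha, and no statement whether success requires one primary or both.

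The Sample size section uses the module "Tests for Two Means in a Stepped Wedge Cluster Randomized Design". Its effect size comes from an earlier study that "reported a mean reduction in depressive symptom of 4.0 in intervention group compared to 2.0 in control group". No remission proportion or odds ratio enters the calculation or appears elsewhere in the article.

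**The concern.** With two primary outcomes, the meaning of a positive trial depends on a rule that the article does not give, and each possible rule conflicts with something the article does state.

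- If a significant result on either outcome is enough, two chances at 0.05 give a family-wise error above 5% unless the two tests are perfectly correlated.
- If both must be significant, the error is controlled, but the 90% power in the Sample size section describes only one of the two requirements.

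The open rule also leaves room to decide after the results are known which outcome carries the claim. That matters more here because the trial is open-label and the outcome is self-reported.

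**Working it through.** **1. The plan's own figure.** Inputs from the Sample size section: 6 communities, 22 per community, 20% dropout. 6 × 22 = 132, and 132 / (1 − 0.20) = 165, as stated. The 90% power cannot be reproduced because no standard deviation is given.

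**2. Error rate if either outcome counts.** For two test statistics that are bivariate normal with correlation ρ, each two-sided at 0.05:

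family-wise error = 1 − P(|Z1| ≤ 1.96 and |Z2| ≤ 1.96).

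| ρ | Family-wise error |
|---|---|
| 0 (independent) | 1 − 0.95² = 9.75% |
| 0.70 | 8.35% |
| 0.75 | 8.10% |
| 0.80 | 7.81% |
| 0.90 | 7.04% |
| 1 (perfect) | 5.00% |

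The article gives no correlation, so ρ has to be assumed. For a normal score and the indicator of lying below its own p-quantile, ρ = φ(z_p) / √(p(1 − p)).

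- p = 0.10: ρ = 0.585, error 8.8%.
- p = 0.20: ρ = 0.280 / 0.400 = 0.70, error 8.35%.
- p = 0.30: ρ = 0.76, error 8.05%.
- p = 0.40: ρ = 0.79, error 7.9%.
- p = 0.50: ρ = 0.399 / 0.500 = 0.80, error 7.8%.

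These values take the correlation of the two test statistics to equal that of the score and its indicator.

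**3. Error and power if both must count.** The probability that both tests are falsely significant cannot exceed that of either one, so the error is at most 5%. In the same way, joint power cannot exceed the lower of the two powers. The article gives a power for the score and none for remission.

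**4. Illustration only: how far the two powers could differ.** Assumptions not in the article: a standard deviation, a control mean, a normal score cut at 4.5, 22 people measured in each community in each of 4 periods, and the Hussey-Hughes variance for 3 sequences of 2 communities with ICC 0.1.

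For SD 4, the variance of the estimated mean difference is 0.372, so the SE is 0.610. The score's power is Φ(2 / 0.610 − 1.96) = Φ(1.32) = 91%. With a control mean of 7, remission is Φ(−0.625) = 26.6% versus Φ(−0.125) = 45.0%. The difference is 0.184, its SE is about 0.073, and power is about 71%.

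| Assumed SD | Score power | Remission power (control mean 8 to 7) |
|---|---|---|
| 3 | 99% | 85 to 90% |
| 4 | 91% | 67 to 71% |
| 5 | 75% | 51 to 53% |

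Remission has the lower power in each row, but the level depends wholly on the assumed inputs.

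**5. Possible remedies at the same N.**

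- Score as single primary with remission gated behind it: error 5%, N stays 165.
- Bonferroni, 0.025 each: error about 4.0 to 4.5% at the correlations in step 2. Power for the score falls from 90% to Φ(1.960 + 1.282 − 2.241) = Φ(1.00) = 84%.
- Both required: error at most 5%, with joint power to be calculated from stated remission rates.

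**The case against.** The strongest reply is that a journal article condenses the full plan, and that testing order and alpha allocation are often left to the SAP. That is fair as far as the missing hierarchy goes. It does not dispose of the point: the article itself designates two primaries, applies one threshold to all tests, and bases the sample size on one of them. An SAP that demoted remission would contradict the Measurement of outcomes section and Table 1.

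A second reply is that both measures come from one instrument at one time point, so any inflation is modest. This is partly right, since the ceiling is 9.75%. At the assumed correlations, however, the error is still more than half as large again as 5%.

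Three stronger readings are tempting, and the documents do not support them.

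- A reader might infer that the primary error rate simply is 8%. It is that only if either outcome can declare success, which the article does not say, and only under an assumed correlation. PHQ-9 is a bounded integer scale, entry requires a score of at least 5, and the tests come from adjusted mixed models, so the normal-score correlation is an approximation.
- A reader might infer that remission is underpowered. The article shows only that its power was not calculated. The illustration above rests on assumed inputs.
- A reader might infer that the exposure-length comparisons and the stepwise model adjustments raise the error further. Extra exposure-length contrasts are possible, but nothing says that each contrast or each model step can declare success, and no such inflation has been quantified.

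**Conclusion.** The point holds in conditional form. The article names two primary outcomes, judges both at 0.05, and leaves the success rule open. If either suffices, the family-wise error is between 5% and 9.75%, and about 8% if the correlation is 0.7 to 0.8 (normal score, remission 20 to 50%). If both are required, the error is at most 5% and the stated 90% power is that of the score alone. Under neither rule do the stated 5% error and 90% power both describe the pair of primaries, except in the limiting case of perfectly correlated tests. It should be corrected, and the correction does not alter the design or the size of the trial.

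**What to change.** Before outcome data are seen:

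- Make the PHQ-9 score at the end of the 12-week intervention the single primary outcome. It is the outcome that the sample size supports.
- Make remission (PHQ-9 below 5) the first key secondary outcome, tested at two-sided 0.05 only if the primary is significant.
- Amend the Measurement of outcomes section and Table 1 accordingly.
- Align the Statistical analyses section, where the sensitivity analyses list the PHQ-9 total score among alternative depression classifications. This would not fit if the score is the sole primary.
- Check the registration and the ethics record, and update them if they list both outcomes as primary.

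Cost: remission alone can no longer carry the primary claim, and a short protocol amendment may be needed. N stays 165. Stating a both-must-succeed rule or splitting alpha would also remove the ambiguity. The first needs a remission power calculation from stated rates. The second lowers the score's power to about 84% at the same N.

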### Participants and recruitment

Participants meeting the following criteria will be included: (1) aged 60 years or above; (2) current depressive symptoms as measured by the Patient Health Questionnaire-9 (PHQ-9) score ≥ 5. The exclusion criteria are: (1) cognitive impairment indicated by a score < 26 on the Montreal Cognitive Assessment (MoCA); (2) contraindications to exercise (e.g., uncontrolled hypertension or diabetes mellitus, unstable angina); (3) current participation in any other intervention program. All participants will provide written informed consent.

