### Randomization and blinding

Initially, all six communities will begin in the control phase. Subsequently, two communities will be randomly allocated to the 12-week intervention period, followed by two other communities 12 weeks later, and the final two communities 12 weeks after that. Trial randomization will be performed by an independent researcher not otherwise involved in the study. Each community will be notified of its own transition date after recruiting first participant but will not be notified of the transition dates of other communities. Details of the randomization schedule are given in Fig. 1.

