### Statistical analyses

Analyses will include descriptive summaries and preliminary unadjusted comparisons between phases (control vs. intervention) and clusters. Specifically, variables within each phase or clusters will be described using descriptive statistics (means and 95% confidence intervals for normal distributed quantitative variables; medians and interquartile ranges for non-normally distributed quantitative variables).

Analyses of data from a SW-CRT requires specific methodological considerations to account for its design, including the control of secular trends (period effects) and the assessment of potential carryover effects. Guided by methodological recommendations for SW-CRTs [60], we will choose Method 3 to evaluate the intervention effects of the integrated exercise-sleep intervention. This method treats the intervention variable as a time-dependent categorical variable, comparing groups with different numbers of intervention measurements with all the control measurements. This allows us to examine whether the effect of the integrated exercise–sleep intervention varies with the length of exposure, thereby informing the time dependency of treatment effects, including potential carryover.

All models will be estimated using multilevel mixed-effects regression to account for the hierarchical structure of the data. We will first fit a two-level (time and individual levels) and a three-level (time, individual, and community levels) mixed-effects model without any potential confounders. Then, we will further adjust the selected model (based on model fit criteria) by including study period (time) as a fixed effect. Third, an adjustment will be made for the baseline value of the outcome variable and associated baseline covariates (e.g., socio-demographics, cognition), and in the fourth step, both an adjustment for the follow-up time, the baseline value of the outcome variable, and related covariates will be performed. To evaluate the time dependency of the effect of starting the intervention, an interaction term between intervention and time can be added to the model [60, 61]. Additionally, we will account for potential between-cluster variations by including relevant community-level covariates (e.g., socio-cultural characteristics and access to health services) as fixed effects in the models, if they show preliminary associations with the outcome.

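### Remission is the complement of the entry criterion, so T0 remission is zero or nearly so by eligibility; nothing keeps T0 out of the control readings, which may inflate the remission odds ratio

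*Protocol article*

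**What the plan says.** All references are to the protocol article.

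- **Participants and recruitment** requires "current depressive symptoms as measured by the Patient Health Questionnaire-9 (PHQ-9) score ≥ 5".
- **Measurement of outcomes** makes remission part of the primary outcome: "The primary outcome will be self-reported depressive symptoms and remission rates, as measured by the PHQ-9 at 12-week post-intervention". It then defines it: "Depression remission is defined as a PHQ-9 score < 5".
- **Table 1** lists "Depression remission rate" under primary outcomes with crosses at T0, 6 weeks and 12 weeks. The eligibility screen stands in an earlier column, before T0.
- **Randomization and blinding**: "Initially, all six communities will begin in the control phase".
- **Statistical analyses** chooses a method described as "comparing groups with different numbers of intervention measurements with all the control measurements", and reports an "odds ratio for binary outcomes between intervention and control periods".
- **Model sequence (Statistical analyses)**: step 1 is a "mixed-effects model without any potential confounders". Step 2 adds study period as a fixed effect. Step 3, as worded, adjusts for the outcome's baseline value and covariates. Step 4 combines follow-up time with the step 3 terms. No step is named as primary.

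The article does not say whether T0 remission is an outcome row, a covariate, or both.

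**The concern.** One cut-off both admits a person and defines remission. A T0 remission reading therefore reflects the eligibility rule and says nothing about how people fare without the intervention. If the PHQ-9 is measured again at T0, a few readings may fall below 5, but the screen still holds the rate down, and someone already below 5 has nothing to remit from.

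The Background expects depressive symptoms to remit spontaneously, so remission should rise after T0 with no treatment at all. All communities start in the control phase, so T0 readings, if used as outcome rows, fall on the control side. They would lower control-phase remission whatever the intervention does, and the odds ratio for a primary outcome could favour the intervention through eligibility alone.

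The covariate use fails as well. Steps 3 and 4 adjust for the baseline value of the outcome, and for remission that value is constant or nearly so.

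**Working it through.** The article gives no remission rate and no odds ratio, so there is no figure of its own to reproduce. The check asks what odds ratio results when the intervention has no effect.

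**Inputs from the article.** Six communities, two crossing over at each of three 12-week steps; entry at PHQ-9 ≥ 5; remission at PHQ-9 < 5.

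**Assumptions.** Readings at weeks 0, 12, 24 and 36; T0 remission exactly 0; the same remission rate *r* at every later reading in both phases, so the true odds ratio is 1. The article gives no value for *r*; 10 to 40% is used. The odds ratios are marginal, without random effects.

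**Formula.** If a fraction *f* of control readings are T0 readings, control remission is *r*(1 − *f*) and

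OR = [*r*/(1 − *r*)] ÷ [*r*(1 − *f*)/(1 − *r*(1 − *f*))] = [1 − *r*(1 − *f*)] / [(1 − *r*)(1 − *f*)].

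**1. Common T0 date, no period term.** The three pairs of communities have 1, 2 and 3 control readings, so there are 2 × (1 + 2 + 3) = 12 community-by-reading control cells. Six are T0, so *f* = 0.5 and OR = (2 − *r*)/(1 − *r*).

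| *r* | Control | Intervention | OR |
|---|---|---|---|
| 10% | 5% | 10% | 1.9/0.9 = 2.11 |
| 20% | 10% | 20% | 1.8/0.8 = 2.25 |
| 30% | 15% | 30% | 1.7/0.7 = 2.43 |
| 40% | 20% | 40% | 1.6/0.6 = 2.67 |

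**2. Common T0 date, period fixed effects.** The fitted odds ratio is 1.00 for every *r*. The T0 period holds only control cells, all zero. Its own effect goes to minus infinity on the log-odds scale and cannot be estimated, but the treatment contrast comes from the later periods and is unaffected.

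**3. Staggered T0 dates, period fixed effects.** Zeros now fall in later periods, in control communities only. Two assumed patterns:

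- A share *f* of 20 to 33% of control rows in the later periods are T0 rows of later enrollees, with *r* of 15 to 30%. Low end: (1 − 0.12)/(0.85 × 0.80) = 1.29. High end: (1 − 0.201)/(0.70 × 0.67) = 1.70.
- One group enrols at week 0 and a second of the same size at the last control reading before crossover. For the first pair of communities these dates coincide, and it has one group. A logistic fit on expected proportions gives 1.83, 1.94, 2.08 and 2.27 for *r* = 10, 20, 30 and 40%. With all communities set to equal size, the values are 1.79, 1.89, 2.02 and 2.20.

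**4. Staggered T0 dates, no period term.** In the second pattern, 5 of 8 control group-readings are T0 (*f* = 0.625), giving 2.85 at *r* = 10% and 3.78 at *r* = 40%.

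**5. T0 rows removed.** The odds ratio is 1.00 in all of these fitted wedge scenarios (the first pattern in item 3 is hand arithmetic, where *f* = 0 also gives 1), with or without period effects.

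**6. T0 as the only control reading.** Table 1 prints T0, 6 weeks and 12 weeks only. If T0 is taken just before the intervention and no control follow-up exists, control odds are zero and the odds ratio cannot be estimated.

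**The case against.** The strongest reply is that the article nowhere states that T0 is a control outcome row. Baseline adjustment in steps 3 and 4 commonly means that T0 is a covariate, the primary time point is 12 weeks post-intervention, and Table 1 lists assessments rather than model rows. Which rows enter a model is often left to a fuller document. Period adjustment is planned and control of secular trends is called necessary; with a common T0 date it removes the bias completely. The bias that survives needs staggered enrolment, which the article leaves open without establishing it, and its size moves with the assumed pattern. A separate T0 visit also means that not every T0 reading need be zero.

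All of this stands as a limit on the claim. It does not settle the matter, because the article itself schedules T0 remission as a primary-outcome reading and fixes the comparator as all control measurements. Step 1, step 3 as worded and the preliminary unadjusted phase comparisons have no period term. Communities learn their transition date after their first participant is recruited, so recruitment may continue and T0 dates may differ. The covariate reading rescues nothing for remission, since a constant adjusts for nothing.

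The lack of an estimable T0 period effect should not be overstated: it affects a nuisance coefficient, not the treatment effect.

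**Conclusion.** The point holds conditionally. The two cut-offs are exact complements, T0 remission carries little or no information, and the plan does not keep it out of the comparator. **If** T0 rows are used as control readings, the null odds ratio is about 2.1 to 2.7 without a period term (common T0 date), about 1.3 to 2.3 with a period term and staggered T0 dates, and 1.00 with a period term and one common T0 date. The later remission rates and the enrolment patterns are assumptions.

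A reader might infer that the plan necessarily inflates the remission odds ratio, or roughly doubles it. The documents do not support that: the use of T0 as a control row is inferred from several sections read together, the largest figures belong to models without period, and enrolment timing is not stated. Nor does the calculation give a false-positive rate for the planned multilevel models.

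Because remission is a named primary outcome and the remedy is nearly free, it should be settled before analysis.

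**What to change.** 1. State that remission is analysed on post-baseline readings only, in every model step, and always with a period term.
2. Use the T0 PHQ-9 score, not T0 remission status, as the baseline covariate in the remission model.
3. Remove the T0 cross for remission in Table 1.
4. Make Table 1 show the control-phase follow-up readings that serve as comparator.

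The cost is analysis wording and a table edit, with little or no remission information lost: none if T0 is the screening reading, and very little if it is a re-measurement. Item 4 is a condition for the rest. If T0 turned out to be the only control reading, dropping it would leave no comparator, and a change of wording would not be enough.

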
To address these gaps, the Geriatric Exercise-Sleep Optimization (GESO) trial protocol was designed by adopting a SW-CRT design. The primary aim is to evaluate the clinical efficacy of an integrated exercise-sleep intervention for alleviating depressive symptoms among community-dwelling older adults, with a particular interest in those with subthreshold depression. Secondary aims are to explore potential underlying mechanisms of the intervention by assessing salivary biomarkers (BDNF and irisin) and EEG; and to evaluate the cost-effectiveness of the intervention from a public healthcare system perspective.

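### The economic evaluation is labelled as taking a public healthcare system perspective, but the costs it describes are only those of delivering the intervention

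*Protocol article*

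**What the plan says.** The Background makes it a secondary aim "to evaluate the cost-effectiveness of the intervention from a public healthcare system perspective", and Measurement of outcomes repeats the perspective: "The economic evaluation will be conducted from a public healthcare system perspective".

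On the cost side, Measurement of outcomes says that the data "will be collected from study records (e.g., personnel time, equipment, materials) and does not impose any additional data collection burden on the participants themselves". Its instrument is a cost form, still to be developed, whose scope is put as: "covers and sums up all GESO-intervention costs and payments that would be reimbursed by health insurance companies if the respective intervention will be accepted", meaning accepted into routine care. The examples of cost elements are trainer wages, room or session costs, documents and programme development. Table 1 has one entry for costs, at 12 weeks.

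On the effect side, QALYs come from the EQ-5D-5L, measured at baseline and 12 weeks, "using the norms for the urban Chinese population". Measurement of outcomes sets the cost-utility endpoint as cost per QALY gained. Statistical analyses plans a CER and an ICER for the cost-effectiveness analysis, but for the cost-utility analysis says only: "CUA will be calculated by QALYs and cost-utility ratio (CUR".

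**The concern.** A healthcare system perspective asks what the system pays in total with the intervention compared with without it. That total includes the care participants use for other reasons, and that care may change in either direction. The costs described here answer a narrower question: what the programme costs to deliver or reimburse.

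The difference matters for this trial. Cost-effectiveness is a named secondary aim, and the Discussion presents the economic results as evidence on scalability. The Background cites earlier work by the same team linking exercise and adequate sleep to lower long-term healthcare spending. A cost total built only from programme items cannot register a saving or an increase in other care.

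Two smaller wording problems affect the QALY side. The two sections describe the cost-utility result differently. And norms are population averages, whereas turning a participant's EQ-5D-5L responses into a utility needs a value set.

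**Working it through.** **Perspective against costs.** The protocol article gives no cost, utility or threshold, so there is no figure to reproduce. The check is a comparison of text.

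| Element | What the article describes | Covers other healthcare use? |
|---|---|---|
| Perspective (Background; Measurement of outcomes) | Public healthcare system | Implied |
| Data source | Study records: staff time, equipment, materials | Not named |
| Cost form | Intervention costs, and payments reimbursable if the intervention were adopted | No; both parts concern the intervention |
| Listed elements | Trainers, rooms, documents, development | No |
| Participant-reported costs | None; no added burden | No |

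**What the omission can do to a ratio.** All inputs in this part are assumptions, chosen only to show scale.

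- Programme cost C = CNY 500 per person.
- Control utility 0.80, constant.
- Utility gain 0.05, rising linearly over 12 weeks.
- QALY gain = (12/52) × 0.05/2 = 0.2308 × 0.025 = 0.00577.
- Incremental ratio = (C + change in other care) / QALY gain.

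| Change in other care (CNY) | Numerator (CNY) | CNY per QALY gained |
|---|---|---|
| Not counted | 500 | 500/0.00577 ≈ 86,700 |
| −300 | 200 | 200/0.00577 ≈ 34,700 |
| +200 | 700 | 700/0.00577 ≈ 121,300 |

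The proportional shift is the omitted change divided by C, whatever the QALY gain: −300/500 = −60% and +200/500 = +40%. At C = CNY 1,000 the shifts are −30% and +20%. Over C of 500 to 1,000 and utility gains of 0.02 to 0.10, the programme-only ratio runs from about CNY 43,000 to 433,000 per QALY gained.

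**Why the form of the cost-utility ratio needs stating.** If CUR were read as total cost over total QALYs, the first set of assumptions gives 500 / [(12/52) × 0.825] = 500/0.1904 ≈ CNY 2,600 per QALY. The incremental figure is about 86,700, which is larger by a factor of 0.825/0.025 = 33. Over the same ranges, with control utility 0.80 to 0.90, the average ratio is about CNY 2,300 to 5,400. The two cannot be used interchangeably.

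**The case against.** The strongest reply is that the article is condensed and the cost form is not yet written. Its lists are illustrative, and the sentence on burden rules out questionnaires but not insurance claims or medical records. That is fair as far as it goes: healthcare use could still be added. But the article does more than stay silent. It names the data source and defines the form by intervention costs and their reimbursement, and it mentions no claims data.

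A second reply is that the Background evidence concerns long-term spending, and that a 12-week comparison in 165 people would not test it. This also stands. The earlier work is a reason to expect that other care may change. It does not make detection of savings an aim of this trial, and it gives no size for any change within the trial.

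A reader might infer three stronger things that the text does not support:

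- *That the QALY result has no comparator.* Cost per QALY gained is an incremental quantity, an ICER is planned for the cost-effectiveness analysis, and CUR is never defined as an average ratio. What remains is a mismatch between two sections.
- *That control-phase cost is zero by construction.* The Interventions section gives control participants weekly contact, which could be costed as staff time. The article does not say whether it will be.
- *That utilities will certainly be wrong.* The cited source for the norms is not at hand, and the word may be a slip for a value set.

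**Conclusion.** The concern holds on the cost side. The stated perspective is wider than the costs described, and the gap runs through every planned ratio. As written, the results could support a statement about the cost of the intervention per unit of effect, but not about net cost to the public healthcare system. The size cannot be known from the documents. On the assumed figures above, moderate changes in other care move the ratio by 20% to 60%, in either direction. The conclusion rests on reading the described data source and cost form as the whole of the cost collection.

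The cost-utility ratio and the word *norms* need correction of wording; neither is a demonstrated error of analysis. The planned discounting might also look out of place in a within-trial analysis, but it does little harm and changes no conclusion: at 5% over 12 weeks the factor is 1.05^(−12/52) = 0.989. It is not part of this point.

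The primary outcome is unaffected.

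**What to change.** Choose one of two routes before data collection, since healthcare use that is not recorded during the trial is hard to recover later.

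1. **Keep the perspective.** Record visits, admissions and medicines in both the control and intervention phases, through a few questionnaire items or claims data, and include them in the cost total. The cost is slight participant burden or work to obtain claims. With questionnaire items, the sentence promising no added burden must change.
2. **Keep the data.** Relabel the analysis as intervention cost only in the Background and Measurement of outcomes, and narrow the scalability conclusion in the Discussion. This is wording only, at the price of a smaller claim.

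Under either route:

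- State in Statistical analyses that the cost-utility result is an incremental cost per QALY, intervention versus control, in line with Measurement of outcomes.
- Replace *norms* with the named Chinese EQ-5D-5L value set, if that is what is meant.

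These two edits cost a sentence each.
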